### 2.7. Interventions

The intervention will be carried out in the nursing classroom of the Faculty of Health Sciences. It will be structured in four face-to-face sessions lasting 2 h each. The process will be led entirely by the PI, who will act as a teacher, clinical facilitator, and administrator of the gamified platform.

Prior to the start of the study, the digital learning environment will be developed: narrative scripts will be generated using generative AI tools. It is important to note that Generative AI is used exclusively offline during the pre-intervention design phase as a drafting tool for the narrative scripts. The AI does not interact with students in real-time, nor does it evaluate their clinical answers. All AI-generated texts are thoroughly reviewed, clinically curated, and validated by the PI prior to their integration into the Wix platform (Wix.com Ltd., Tel Aviv, Israel) to prevent any clinical hallucinations or biases. In the CG, the narrative will be linear and generic for each topic. In the EG, there will be five narrative variations per theme, adapted to the profiles of the PPDS (Tryhard, Coacher, Esthetic, Joker, and Toxic). To clarify the specific elements of adaptation and ensure reproducibility, Table 1 details the differences between the generic and adapted narratives. It is important to note that the level of clinical difficulty and the learning objectives remain invariant between groups to ensure the validity of the academic performance comparison: patient vital signs, clinical history, learning objectives, and multiple-choice questions are identical in both groups. The adaptation focuses exclusively on the narrative ‘wrapping’, the tone of the feedback, and the motivational mechanics (gamification elements) triggered by the Wix platform.

A master website will be set up on Wix. Progress will be managed through “Digital Locks”, where students will be required to solve clinical issues embedded in Google Forms. Upon submitting the correct answer, the form will return a password that will allow the student to unlock the next page (level) in Wix.

The total cohort of 38 students will be divided into two consecutive practice shifts (Group A and Group B): one with 18 students and the other with 20. In the first session, software will be used to randomly assign which group will have the first shift. Students will remain in their assigned group for all four sessions to avoid cross-contamination. The program consists of four compulsory thematic modules:-Session 1: Prenatal care;-Session 2: Maternal-fetal assessment and well-being;-Session 3: Obstetric risk triage;-Session 4: Critical management in pregnancy.

Each day of the internship follows the same 120 min (2 h) time structure, which is visually summarized in Figure 2.

During the middle 60 min (intervention), the PI will monitor activity as the students interact with their devices. In the CG, all learners receive the same login URL and password, and the storytelling in Wix is standard. The mechanics are the same for everyone: progress bars are present, and points are awarded for correct answers. In the EG (PPDS-Adapted Gamification), at the beginning of each session, the PI provides differentiated codes (according to role) based on the learner’s profile to access five parallel narratives in Wix for the same clinical case. The clinical goal is the same for all participants, but the narrative “wrapping” and side mission change.

To ensure fidelity, the PI will be the only person with admin privileges in Wix and access to the Google Forms answers in real-time. Attendance will be monitored using signatures. The PI will resolve technical or clinical questions during the session, ensuring that the password lock in Wix does not impede the progress of learning.

Forms will be set up as “required steps” within the Wix narrative. In the case of the EG, the knowledge forms will be identical in content but esthetically matched to the identified player’s profile.

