### 2.5. Randomization and Masking

Given the nature of practical teaching (in which groups are pre-established by enrollment), simple individual randomization is not possible. Therefore, a cluster randomization design will be implemented. An independent researcher not involved in the teaching process will use (RANDOM.ORG; Randomness and Integrity Services Ltd., Dublin, Ireland) computerized random number generation software to assign the practice shifts (clusters) to either the CG or EG arm. Allocation concealment is ensured as the assignment will only be revealed to the Principal Investigator and students on the first day of the intervention.

Given the highly experiential nature of the intervention, participant blinding to the educational differences between conditions is likely only partial. However, participants will remain naive to the comparative study hypothesis and their specific allocation to either the control or experimental cohort. However, due to the logistical requirements of the intervention (the distribution of specific login codes), the Principal Investigator (PI) cannot be blinded during the sessions. To mitigate bias and ensure external control, statistical data analysis will not be performed by the PI. Instead, it will be performed by a different researcher (the co-author) who was not involved in the teaching process, using a dataset in which the group assignment is masked (coded as Group A vs. Group B).

To maintain this blinding and prevent the participants from distinguishing between the narrative formats (generic vs. adapted), the intervention relies on the physical and temporal separation of the clusters. Since Group A and Group B attend consecutive but distinct shifts, there is no simultaneous visual contact with the screens of the Control and Experimental groups. Furthermore, the clinical content and the structure of the Google Forms (Google LLC, Mountain View, CA, USA) remain visually identical for both groups; only the Wix interface ‘wrapping’ differs, and this is not visible to the other group due to the shift separation.

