### 2.8. Outcome Variables

The main outcome variable will be academic performance, LG, understood to reflect new knowledge acquired on the subject under study. The degree of assimilation of the theoretical and practical concepts of pregnancy and childbirth in each of the four clinical cases will be evaluated. To this aim, an “ad hoc” questionnaire comprising 40 multiple-choice questions was designed by the PI, who is a certified Nurse Specialist in Obstetrics and Gynecology (Midwife) and the lecturer in charge of the class. The items were constructed to strictly align with the specific curricular contents and learning objectives of the ‘Reproductive Health’ syllabus. To ensure external content validity prior to administration, this initial draft will be reviewed by an external panel of five experts (three academic midwives and two obstetricians). Regarding reliability, since this is a pilot study, internal consistency and item analysis will be calculated post hoc to validate the instrument for future trials. The questions in the final questionnaires (administered post-simulation at each session) will address the same content as the initial questionnaire, but the form and order of the answers will be modified. Learning gain will be calculated using a simple difference (post-test score minus pre-test score), normalizing the results on a scale of 0 to 10 points. An arithmetic mean of the learning gain scores obtained from the four use cases will be calculated.

The secondary outcome variables will be

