As the researcher is also the teacher who evaluates the coursework, this could introduce unconscious bias (Pygmalion Effect) to favor the EG or generate in the students a desire to please the teacher by responding positively to the surveys. To address this situation, the knowledge-assessing questionnaires contain multiple-choice questions to facilitate automatic and objective correction and eliminate subjectivity on behalf of the evaluator. Anonymity will be guaranteed for the satisfaction surveys to encourage honesty.

As for the profile self-evaluation through the PPDS, the classification of the students depends on their sincerity when answering the test. It may be that a “Toxic” student does not recognize themselves as such and marks “Coacher” answers due to social desirability, thus being assigned a narrative that does not correspond accurately to their profile. This issue will be addressed by clearly explaining that there are no “good or bad” profiles, thus reducing social pressure.

Another limiting aspect is the risk of contamination between groups. As students are classmates from the same faculty, the CG students may learn about the existence of the EG’s “special missions” and feel demotivated (demoralizing effect) or try to obtain the EG passwords. To address this issue, Wix login passwords will be changed on a per-session and group basis, and explicit confidentiality will be required as part of the “game contract”. To actively monitor this risk without increasing survey fatigue, the Principal Investigator will utilize the pre-established “field diary” to record any spontaneous student disclosures or observable evidence of cross-contamination between the shifts. Any detected contamination will be reported as a feasibility metric and factored into the interpretation of the exploratory efficacy results. While this observational approach is suitable for a pilot, future definitive trials will benefit from incorporating a formal self-report question to empirically measure cross-contamination rates.

Finally, as a logistical limitation, and given the nature of the study, failures in the faculty’s Wi-Fi connection, Wix server crashes, or problems with students’ mobile devices could interrupt the intervention. An alternative plan will be available, with changes in the teaching schedule agreed upon with the students so that a new practical session may be scheduled.

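### Live clinical help from the unblinded PI, who wrote the test, can differ by arm and enter Learning Gain; the stated remedy for teacher expectancy covers marking only

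*Protocol article*

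**What the plan says.** Section 2.5 (Randomization and Masking) states that "the Principal Investigator (PI) cannot be blinded during the sessions". Another researcher analyses a dataset with coded arms.

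Section 2.7 (Interventions) gives the PI sole charge of delivery in both arms: "The process will be led entirely by the PI, who will act as a teacher, clinical facilitator, and administrator of the gamified platform". Progress depends on digital locks: "Upon submitting the correct answer, the form will return a password that will allow the student to unlock the next page". The PI alone has real-time access to the lock answers. On help, the section says: "The PI will resolve technical or clinical questions during the session". The stated purpose is that a lock should not hold up learning. The section fixes the clinical case, learning objectives and test items as identical between arms. It gives no rule on the content or amount of the PI's help.

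Section 2.8 (Outcome Variables) says that the primary-outcome "questionnaire comprising 40 multiple-choice questions was designed by the PI", with content review by five external experts. The final questionnaires are "administered post-simulation at each session". LG is post-test minus pre-test on a 0 to 10 scale, averaged over the four sessions.

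Section 4.1 (Limitations) acknowledges that the teacher-researcher role could produce a Pygmalion effect in favour of the experimental group. For the knowledge outcome its answer is that the questionnaires "contain multiple-choice questions to facilitate automatic and objective correction and eliminate subjectivity on behalf of the evaluator". It adds anonymity, but for the satisfaction surveys.

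**The concern.** The protocol names a bias and then says that it is dealt with by a measure acting at a different point. A teacher's expectancy can work through what is explained, to whom and how fully, before any test is marked. If one shift receives more or better explanation of the tested material, its post-test scores rise and objective marking counts the rise as learning.

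An LG difference could then partly reflect live help rather than the adapted narrative. The generic comparator was chosen in the Introduction to isolate the value of personalization. Sections 2.4 and 2.10 make the effect size the main statistical product, to be used in the power calculation for a later trial. Calling the tests exploratory does not protect that estimate from a shift in its centre.

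**Working it through.** **Step 1. Which safeguards reach live help?** The measures in the protocol article, and where each acts:

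- Objective multiple-choice marking (4.1): acts at scoring, after the help has been given.
- Masked analysis by another researcher (2.5): acts after the data exist.
- Analysis only after transcripts are locked (2.11): protects official grades.
- Anonymity (4.1): concerns the satisfaction surveys, not LG.
- Identical cases, objectives and items (2.7): standardises the platform and the test, not what the PI says.
- Expert review of the items (2.8): concerns content validity.
- Field diary (2.9, 2.11, 4.1): records reasons for missing data, distress, technical incidents, dissatisfaction and contamination, not help given.

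None limits, standardises or records clinical help by arm.

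**Step 2. Could help differ without deliberate favouritism?** Yes. In the control group the PI supports one narrative; in the experimental group, five parallel narratives with side missions (2.7, Table 1). The shifts are consecutive (2.5), so the second meets a PI who has just heard the first shift's questions. Neither fact gives a direction.

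**Step 3. Scale.** The plan gives no power, target effect or SD for LG, so there is no figure of its own to reproduce. Everything below is illustrative.

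Inputs from the document: 40 items, four sessions, 0 to 10 scale, arms of 18 and 20. Assumptions: half an extra correct item per student per session in one arm; LG SD of 1 to 2 points. Section 2.8 does not say how the items are divided between sessions, so both readings are shown.

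Shift per session = 10 × (extra items) / (items per session test). A shift that recurs in all four sessions is unchanged by averaging: (4 × shift) / 4 = shift.

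- 10 items per session (40 / 4): 10 × 0.5 / 10 = 0.5 point. 0.5 / 2 = 0.25 SD; 0.5 / 1 = 0.50 SD.
- 40 items each session: 10 × 0.5 / 40 = 0.125 point. 0.125 / 2 = 0.0625 SD; 0.125 / 1 = 0.125 SD.

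**Step 4. Against the noise of this trial.** With individuals as the unit, ignoring clustering and using a normal approximation, the standard error of the difference is √(1/18 + 1/20) = 0.325 SD. Two-sided p = 0.05 (sidedness assumed) is reached at 1.96 × 0.325 = 0.64 SD. With no true effect and a shift of b SD, the chance of p < 0.05 is Φ(b/0.325 − 1.96) + Φ(−b/0.325 − 1.96):

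- b = 0.25: 12%; b = 0.50: 34%.
- b = 0.0625: 5.4%; b = 0.125: 6.7%.

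On the first reading the assumed shift matters for the estimate and for the false-positive rate. On the second it is close to negligible.

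**The case against.** The strongest reply has four parts.

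First, the help instruction is the same for both arms and one teacher gives it, so there are no between-teacher differences. That is true, but the teacher knows the arm, so equal help cannot be assumed.

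Second, help with a lock is not help with the test. Section 2.9 separates the digital locks from the paper knowledge tests, and Section 2.8 has the form and order of the answers changed at post-test. This weakens the route without closing it, since locks and tests concern the same clinical topics.

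Third, Section 4.1 already concedes that one cluster per arm may confound the effect and that efficacy comparisons are exploratory. This stands: the point is one further source of bias, and removing it would leave the cluster confounding in place.

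Fourth, the size has no anchor in the documents. This also stands.

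Three stronger readings are tempting and not supported. A reader might infer that the help falls in the hour directly before each post-test, because Section 2.7 says "During the middle 60 min (intervention), the PI will monitor activity as the students interact with their devices" and the test comes after the simulation. The session workflow is in Figure 2, which is not shown, and a debriefing may lie between. A reader might also infer that Section 2.7 contradicts itself by claiming that only the narrative wrapping differs. That section also lists feedback tone and motivational mechanics as adapted, and it describes the material, not the PI's conduct. Finally, a reader might infer that LG will be biased towards the experimental group. The protocol acknowledges that possibility; nothing in it shows that this will happen.

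**Conclusion.** The point holds as a mismatch between a named risk and its stated remedy. Teacher expectancy is acknowledged; for LG it is met by objective marking, and masked analysis adds protection at the analysis stage. Neither reaches live clinical help from an unblinded test author, given in the same session as the post-test. That help can differ by arm, and any difference would enter the effect size meant for the next trial.

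The illustrated size is 0.25 to 0.50 SD with 10 items per session, or about 0.06 to 0.125 SD with 40, resting on an assumed half item of extra help and an assumed SD of 1 to 2 points. The mismatch itself does not depend on these figures. Because the main confounding is already conceded and the direction is unknown, this is a cheap improvement and not a flaw that invalidates the pilot.

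**What to change.** In Section 2.7, state one help rule for both shifts. For each digital lock, prepare written hints with identical text in both shifts, composed before the allocation is revealed. Use them as the first response to clinical questions about the locks. The PI may still help further where a lock would otherwise stop a student, which keeps the facilitator role that Section 2.7 describes. Holding all clinical questions until after the post-test is not needed and would conflict with that role.

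Tally hints and any further clinical help by session and shift in the existing field diary, and report the counts beside LG.

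In Section 4.1, say that multiple-choice marking removes scoring bias only, and list residual unequal teaching help as a limitation.

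The cost is a short hint sheet per session, a few lines of text and a running tally. The tally would be kept by the unblinded PI while supervising 18 to 20 students, so it describes the help given but is not an independent check on it.

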### 2.8. Outcome Variables

The main outcome variable will be academic performance, LG, understood to reflect new knowledge acquired on the subject under study. The degree of assimilation of the theoretical and practical concepts of pregnancy and childbirth in each of the four clinical cases will be evaluated. To this aim, an “ad hoc” questionnaire comprising 40 multiple-choice questions was designed by the PI, who is a certified Nurse Specialist in Obstetrics and Gynecology (Midwife) and the lecturer in charge of the class. The items were constructed to strictly align with the specific curricular contents and learning objectives of the ‘Reproductive Health’ syllabus. To ensure external content validity prior to administration, this initial draft will be reviewed by an external panel of five experts (three academic midwives and two obstetricians). Regarding reliability, since this is a pilot study, internal consistency and item analysis will be calculated post hoc to validate the instrument for future trials. The questions in the final questionnaires (administered post-simulation at each session) will address the same content as the initial questionnaire, but the form and order of the answers will be modified. Learning gain will be calculated using a simple difference (post-test score minus pre-test score), normalizing the results on a scale of 0 to 10 points. An arithmetic mean of the learning gain scores obtained from the four use cases will be calculated.

The secondary outcome variables will be

-Satisfaction: The students’ subjective perception of the usefulness, fun, and motivation generated by the activity will be evaluated using the Gameful Experience Scale (GAMEX) [28]. This validated 27-item instrument in Spanish is suitable for measuring game experience in nursing students’ training. It uses Likert-type responses to measure the multidimensional nature of the gamified experience in the educational context. The six dimensions include enjoyment, abstraction, creative thinking, activation, absence of negative effects, and mastery. This model demonstrated high overall reliability, with a Cronbach’s alpha of 0.85. The scoring format uses a five-point Likert scale. In the proposed study, measurement will be conducted exclusively at the end of the intervention (Session 4) to capture the students’ overall perception of the program. Prior to analysis, items with negative wording (reverse punctuation) will be recoded so that higher scores consistently reflect a more positive experience. The statistical report will present results for both the total aggregate score and the independent mean scores for each of the six dimensions.-Player Profile: the students’ psychological and behavioral predisposition to game dynamics and narratives will be assessed using the PPDS in its validated Spanish version [21]. The PPDS is a psychometrically validated instrument composed of 21 items rated on a six-point Likert scale specifically designed to identify player profiles in the context of educational gamification based on narratives to measure the frequency of certain behaviors, where 1 means “Never” and 6 means “Always”. After a student completes the questionnaire, the system does not place them in a single category but generates five independent scores, one for each profile, showing which of the following profiles they align with the most: Tryhard (achievement- and competency-oriented); Coacher (oriented toward leadership and help); Esthetic (narrative and visual beauty-oriented); Joker (oriented to humor and surprise); or Toxic (a technical gamification term referring to players oriented toward testing system limits, seeking loopholes, or disrupting boundaries, often associated with lateral thinking rather than a negative personal judgment). The scale demonstrated high overall reliability (omega = 0.93).-Gamification Experience: Previous experience in gamification will be evaluated using the following question: Have you participated in similar activities before? The students can respond “yes” or “no”.-Sociodemographic variables: Age is understood as the time that a person has lived, counting from birth to the time of the survey, measured in whole years; gender is understood as a variable that refers to the social and cultural construction that defines the roles, behaviors, activities, and attributes that a society considers appropriate, with the answer options male, female, and non-binary; and the average grade considered to mean the average grade achieved in the first year of the nursing program to monitor the differences between the groups.-Feasibility and implementation outcomes: given the pilot nature of this trial, the following feasibility metrics will be formally tracked to inform the design of the subsequent definitive trial: recruitment rate, retention rate, technical failure rate, time-on-task compliance, and qualitative evidence of cross-contamination.
